# **v) Neonatal immunization**

As newborns are particularly susceptible to infectious diseases, the World Health Organization (WHO) has identified neonatal vaccination as a research priority, in particular the quality of Th1 versus Th2 responses to existing vaccines (see vii below) and induction of appropriate systemic and mucosal immune responses. In neonatal immunization, assessment of antibody alone may be misleading as maternally derived antibody interferes with vaccine-induced antibody production but does not inhibit T-cell responses and priming of memory B-cells (36). Neonatal hepatitis B and BCG immunization is safe and effective in developing countries with high coverage. Data on neonatal immunization with polysaccharide-protein conjugate vaccines is limited to ~200 neonates given Hib conjugate vaccines, which were well tolerated with evidence of priming after a single dose (47, 48). Neonatal immunization with Hib conjugate vaccines with tetanus and CRM197 carrier proteins does not affect Hib or carrier protein antibody responses post-primary immunization, but the Hib-meningococcal OMP conjugate vaccine (PRP-OMP) is associated with a decreased response to subsequent PRP-OMP vaccination, suggesting induction of hyporesponsiveness (49). The mechanism for this is unclear as there was no evaluation of T-cell responses. In view of the high mortality from IPD in infancy and to achieve optimal vaccine coverage, an expert WHO committee has recommended evaluation of PCV neonatal immunization (50). Prior to larger-scale efficacy studies of neonatal PCV in high-risk groups, the safety and immunological feasibility of this approach must be established. In addition to serum responses to Pnc antigens, assessment of mucosal Pnc antibody is important, given the role of IgA in prevention of Pnc carriage and mucosal infections, including pneumonia. Neonatal PCV vaccination must also consider potential effects on postnatal maturation of the immune system, in light of recent concerns regarding non-specific effects of immunization on mortality in African children (51) – increased mortality with DTP in African but not PNG children (33) but reduced mortality with measles and BCG vaccines in both populations. These findings highlight the need for detailed evaluation of non-specific effects of new vaccines and new schedules on the maturation of humoral and cellular immunity during infancy (see vii/viii below).

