# **iv) Specimen collection**

This study will involve collection of cord blood and a total of 6 blood samples over the first 18 months of life (3 samples before 6 months). Nurses at PNGIMR have extensive experience in venepuncture for culture and immunogenicity studies in young infants (5, 76). Preparation of PBMCs also allows for collection of 1.5-2ml plasma, which will be defibrinated and used for serological assays (IgG subclasses, OMP IgG) if insufficient serum is collected. This has been validated in our laboratory and defibrinated plasma is the source for the WHO pneumococcal QC sera. All specimens will reach the laboratory within 2 hours.

*Serum* (2-4ml) will be taken at birth (cord), 2, 3 and 4 months of age (initial responses to 1, 2 and 3 doses of PCV), 9 and 10 months (pre- and post-PPV booster) for memory to PCV serotypes, and for antibody persistence at 18 months.  Pnc serotype-specific IgG antibodies in serum will be measured on all samples. CPS IgG and IgG subclasses will also be measured. *Heparinised blood* (3-5ml) will be collected for T-cell cytokine studies from cord blood and at 3, 9, 10 and 18 months of age to examine development of Pnc and vaccine-specific immunity as well as overall development of Th1/Th2 immunity. This amount of blood has proven sufficient in previous studies by our group (65) for the assays proposed.

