### vi) Specific scientific questions

1.  *Safety and immunogenicity of PCV under an accelerated 1-2-3 month schedule in PNG infants*

PCV has been shown to be safe and efficacious against IPD in SA infants given at 6-10-14 weeks of age ([name], pers comm). The standard PNG immunization schedule is at 1-2-3 months of age to achieve optimal vaccine coverage. PNG infants have higher Pnc carriage rates than reported in SA infants, which may affect immune responses to PCV. It is important that the reactogenicity and immunogenicity of PCV be established in this population at 1-2-3 months of age in comparison to control infants receiving the standard PNG infant immunizations. The response in SA infants after 1 and 2 doses of PCV at 6 and 10 weeks respectively suggests that fewer than 3 doses may be necessary in some populations (43). Therefore antibody responses to 1 and 2 doses will be examined. Immunogenicity will be primarily assessed by serotype-specific serum IgG at 2, 3 and 4 months of age, in comparison to responses in infants not receiving PCV.

2. *Safety and immunogenicity of neonatal immunization with PCV in PNG infants and comparison with early infant immunization*

Should infants be able to mount appropriate immune responses to PCV in the first week of life, then neonatal PCV should result in earlier protection against IPD due to vaccine serotypes and may provide protection against early carriage. Though neonatal responses to PCV may appear modest because of maternal antibody present, conjugate vaccines may still prime for memory (36). For our primary outcome, serum Pnc serotype-specific IgG antibody at age 2 months will be compared between neonatal PCV and control groups. This will assess whether there is a booster antibody response to the second dose of PCV in the neonatal group compared to infants given their first dose at 1 month of age and to naturally acquired antibody levels in the control group. This will determine whether neonatal PCV results in earlier protection, and monitoring will show whether safety has been compromised. We note that a safe and equally immunogenic outcome would be a more favourable response to neonatal PCV, since neonatal administration has the major logistic advantage of increasing uptake of the vaccine in the population.

*3. Induction of immunologic memory by neonatal and early infant PCV in PNG infants*

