# **viii) Data analysis**

The principal analyses of efficacy and safety will be based on t-tests and chi-square tests. Further analyses examining the association of different factors such as number in household, housing type, town/country etc with response will use multiple regression methods: linear when IgG or cytokine level is the response, logistic when IgA, carriage or cytokine detection is the response, Cox when time to hospital admission or onset of carriage is the response, or Poisson when admission rate is the response.

Comparison of cytokine levels between the different groups at different times will employ the same basic methods; however, further analyses of immune competence will be slightly more complex in that the profile of within-person changes over time in antibody and cytokine levels will form the major response and explanatory variables. Thus 2-level models allowing for different levels of variability within and between children will be used, comparing in particular both level and rate of change of these measures. These regression models will also include terms for vaccination status as well as the other confounders such as crowding, sex etc.

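### The principal antibody comparison is left unadjusted for cord-blood IgG, a baseline the protocol already measures and says matters: a loss of efficiency, not of validity

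*Protocol*

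**What the plan says.** The data analysis section (viii) of the protocol fixes the principal method: "The principal analyses of efficacy and safety will be based on t-tests and chi-square tests". Regression comes in only for further analyses. The factors named there are household size, housing, town or country, crowding and sex. Cord IgG is not among them, although the list is open-ended. The same section plans 2-level models of within-person antibody and cytokine profiles, again as further analyses.

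The primary outcome is set in section vi, question 2: "For our primary outcome, serum Pnc serotype-specific IgG antibody at age 2 months will be compared between neonatal PCV and control groups".

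The baseline value is part of the sampling plan. Under specimen collection (iv), serum "will be taken at birth (cord), 2, 3 and 4 months of age", and "Pnc serotype-specific IgG antibodies in serum will be measured on all samples". Table 2 marks capsular IgG at birth for all nine serotypes assayed.

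The protocol also says why that value matters. The neonatal immunization section (v) states that "maternally derived antibody interferes with vaccine-induced antibody production". The paragraph that names the primary outcome says: "Though neonatal responses to PCV may appear modest because of maternal antibody present".

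**The concern.** The plan identifies a variable that bears on the primary outcome, measures it in the trial, and then leaves it out of the primary comparison. IgG at 2 months is the sum of what the infant has made and what remains of maternal IgG. If cord IgG explains part of the spread between infants, an unadjusted t-test carries that spread in its standard error. It also leaves in the estimate any chance difference in maternal antibody between the groups. At stake are the width of the confidence interval for the primary comparison and how far one realised randomisation can move the estimated ratio. The choice is written into the protocol, so it is more than a detail left open for a later document.

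**Working it through.** **Inputs from the protocol (section vii).** SD of log IgG about 1 (natural log), at all ages; 80% power; 5% significance (sidedness not stated, two-sided used here); 100 per group with at least 90 evaluable; reference seroprotection 70%.

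**Input not in the documents.** The within-group correlation ρ between log cord IgG and log 2-month IgG. It is assumed and shown as a range.

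**Step 1: the plan's own figures.** With a pooled-variance two-proportion test, power for 70% versus 50% is 78.7% at 90 per group and 82.8% at 100. For 70% versus 90% it is 92.5% and 94.8%. The exact 95% CI for 70% is 60.0–78.8% at n = 100 and 59.4–79.2% at n = 90. The stated 80% power and 60–79% interval are reproduced in essence.

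**Step 2: unadjusted t-test on log IgG.** Detectable difference = (1.960 + 0.842) × √(2/90) = 2.802 × 0.1491 = 0.418 ln units. exp(0.418) = 1.52.

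**Step 3: adjustment for cord IgG, same slope in both groups.** Residual variance is 1 − ρ². The detectable difference is 0.418 × √(1 − ρ²), the equivalent unadjusted n is 90/(1 − ρ²), and power for the original 0.418 is Φ(2.802/√(1 − ρ²) − 1.960).

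| ρ (assumed) | Variance reduction | Detectable ratio | Equivalent n per group | Power for 0.418 |
|---|---|---|---|---|
| 0 | 0% | 1.52 | 90 | 80.0% |
| 0.2 | 4% | 1.51 | 94 | 81.6% |
| 0.3 | 9% | 1.49 | 99 | 83.6% |
| 0.5 | 25% | 1.44 | 120 | 89.9% |
| 0.7 | 49% | 1.35 | 176 | 97.5% |

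**Step 4: chance imbalance.** In SD units, the difference in mean log cord IgG between two groups of 90 has standard deviation √(2/90) = 0.149, so its 95% limit is 1.96 × 0.149 = 0.292. Left unadjusted, an imbalance of that size moves the estimated ratio by exp(0.292ρ): 1.06, 1.09, 1.16 and 1.23-fold at ρ = 0.2, 0.3, 0.5 and 0.7.

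**Step 5: slopes that differ between groups.** Residual maternal IgG implies a positive slope in controls. Interference with the vaccine response implies a flatter or negative slope in the neonatal group. With equal groups, a common-slope model reduces variance by the square of the average slope. Slopes of +0.5 and −0.3 average 0.1, so the reduction is 1%. A simulation of 4,000 trials gave an adjusted-to-unadjusted variance ratio of 0.999 for that pair and 0.93 for slopes of +0.5 and 0. Even for +0.5 and −0.5 it was 1.005, so adjustment cost practically nothing.

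**Step 6: which other terms belong in the model.** From the allocation schema in section vii, group 1 has 0, 52 and 52 infants in block 1, block 2 and blocks 3–4; group 3 has 26, 26 and 52.

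- Urban/rural: each group has 52 infants in each stratum. The information is 2 × (52 × 52/104) = 52, the same as unstratified (104 × 104/208 = 52), so this term costs nothing.
- Block: the information is 0 + 52 × 26/78 + 52 × 52/104 = 17.33 + 26 = 43.33. The variance rises by 52/43.33 = 1.20, that is 20% in a two-group model. The ratios in step 3 would not describe a model that includes block.

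**The case against.** The strongest reply is that nothing here is an error. As far as cord IgG is concerned, randomisation protects the unadjusted t-test. The trial is sized on the unadjusted SD of 1, so planned power does not depend on adjustment. Covariates are commonly settled in an analysis plan, which is not shown. The first two points stand, and they limit this to a question of efficiency. The third stands only in part, because the protocol itself names the principal tests.

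The size of the benefit is also open to challenge. A reader might infer that cord IgG must be the dominant predictor of the 2-month level. The documents do not say so. The section on natural immunity says maternal antibody lasts a shorter time in settings such as PNG, which points to a possibly low correlation. The protocol's own interference mechanism could also set opposing slopes in the primary comparison and cancel the gain (step 5). Both points stand.

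A reader might further infer that cord IgG is ignored throughout. It is absent only from the principal analyses: the planned 2-level models could use it, and the covariate list is open.

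Finally, it is tempting to add block as well. Block 1 has no neonatal-group infants, so block adjustment concerns non-concurrent controls. It has its own variance cost and is not part of this precision gain.

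**Conclusion.** The point holds as a matter of efficiency. The protocol fixes unadjusted principal tests although it measures, and calls relevant, a baseline that could sharpen the primary comparison. The stronger reading, that the t-test is invalidated by leaving cord IgG out or that planned power is lowered, is not supported.

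The gain cannot be read from the documents. It rests on SD 1, 90 evaluable per group, two-sided 5%, and an assumed correlation common to both groups. Under those assumptions the detectable ratio falls from 1.52 to between 1.49 (ρ = 0.3) and 1.35 (ρ = 0.7), with variance lower by 9% to 49%. At ρ of 0.2 or less the gain is under 2 power points. With opposing slopes in groups 1 and 3 it may be close to nil. Because the groups are near equal in size, adjustment does not lose precision in large samples, so the change is worth making even with the benefit uncertain.

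**What to change.** Reword the principal antibody analysis in section viii as a linear model of log IgG on group, log cord IgG of the same serotype and urban/rural stratum. Keep the t-test as a sensitivity analysis. Report a model with a cord-by-group term as a check on whether the slopes differ.

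For the 0.5 threshold, fit a model with the same terms and report a standardised difference in proportions. An adjusted odds ratio would be a different quantity from the 20-point difference on which section vii is powered.

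Fill the missing cord values by simple imputation, for example the overall mean of log cord IgG for that serotype. There should be few of them, because the recruitment section makes entry depend partly on obtaining a cord sample, although home births may be included. Treat adjustment for block as a separate decision.

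The cost is wording and a little programming. The cord assay is already planned, and no visit, sample or sample-size figure changes.

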The amount of serum (or plasma) and saliva available may limit the number of additional serological investigations that can be performed. A summary of assays proposed at each time point is shown in Table 2. At least 4 representative serotypes will be selected for each assay to allow correlation between assays for serotype- specific results. These include PCV serotypes 6B, 14 and 19F (all common carriage isolates and causes of IPD in PNG) and non-PCV serotype 7F, which is the most common cause of IPD in young PNG infants (79). Antibody avidity for CPS IgG antibodies will be assessed in PNG using a modified elution ELISA with the chaotrope, sodium thiocyanate (NaSCN) as described (80) with modifications for the WHO Pnc ELISA. Avidity index is the concentration of NaSCN resulting in a 50% reduction in OD. Serotype-specific Pnc IgG1 and IgG2 subclass antibodies will be assayed in sera (or defibrinated plasma) at selected time points by standardised ELISA with 89SF reference sera as above with substitution of appropriate monoclonal enzyme conjugate. Serum IgG responses to Pnc OMPs PspA, PsaA and Ply will also be measured by ELISA as described (57).

Salivary ELISA methods that have been established (through collaboration with [name]’s laboratory) to measure IgA responses to selected CPS serotypes (6B, 7F, 14, 19F) (44), and Pnc OMPs, PspA, Ply and PsaA (58), on samples as shown in Table 2. Pnc salivary IgA will be expressed as percentage of total salivary IgA. The low CPS antibody concentrations in saliva and limitations on the amount able to be collected will mean that only CPS or Pnc OMPs will be measured at time points <10 months of age (Table 2).

##

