PNG infants remain at ongoing risk of IPD in the first 5 years of life. Long-term protection induced by PCV depends on the successful priming for immunologic memory so infants can mount brisk anamnestic antibody responses on subsequent challenge. All infants will receive 23-valent PPV at 9 months of age (6 months after their primary course) to evaluate the induction of memory to PCV serotypes. These serotypes in PPV are not immunogenic in PNG infants at age 9 months (except for 23F) (24) so that significant IgG responses to PCV serotypes compared to PCV-naive controls will indicate the induction of memory. This vaccine is efficacious from age 6 months and provides some cover against serotypes which are important causes of IPD in this population. Antibody avidity maturation (post-primary to post-booster immunization) will also be assessed as it is a surrogate marker for the induction of memory after conjugate vaccines (39, 80, 81) and influences the functional capacity of antibodies produced (35). Avidity maturation will be assessed by comparing changes in avidity index between 4-, 9- and 10-month samples in comparison to controls. Antibody persistence will be evaluated with blood samples at 18 months of age.

*4. The impact of neonatal versus early infant vaccination upon nasal carriage of pneumococci*

Reduction in the burden of early Pnc carriage in the critical neonatal period may have an important impact on early disease as well as the development of long-term immunity to Pnc infections. Regular carriage sampling in the first month of life will assess the impact of neonatal PCV immunization, and carriage will be assessed at regular intervals thereafter to determine persisting effects of PCV on carriage compared to controls.

*5. The impact of early colonisation with vaccine serotypes on antibody responses (systemic and mucosal) to neonatal and early infant immunization with PCV*

In the Asaro Valley 60% of infants acquired Pnc in the URT by 15 days of age. PCV serotypes are responsible for 59% of carriage isolates in the first 3 months of life in PNG (16). Swabs will be collected at weekly intervals during the first month to identify children with early ( 2 weeks) colonisation. This will allow evaluation of the effects of early colonisation on systemic antibody responses to subsequent PCV immunization. Effects of time of colonisation and PCV on mucosal immunity (salivary IgA responses to Pnc CPS and OMPs) will also be assessed .

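### The covariate regressions name only a logistic model for salivary IgA, although it is recorded as a continuous percentage and cytokines get both a level and a detection model

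*Protocol*

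**What the plan says.** Under Laboratory methods (section v) the protocol states the scale of the measurement: "Pnc salivary IgA will be expressed as percentage of total salivary IgA". The same paragraph notes "The low CPS antibody concentrations in saliva and limitations on the amount able to be collected" as a constraint on what can be assayed before 10 months.

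Under Data analysis (section viii) there are three layers.

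- Main tests: "The principal analyses of efficacy and safety will be based on t-tests and chi-square tests".
- Covariate models: "Further analyses examining the association of different factors such as number in household, housing type, town/country etc with response will use multiple regression methods". Within that sentence the model is "linear when IgG or cytokine level is the response" and "logistic when IgA, carriage or cytokine detection is the response". Cox and Poisson models follow for times and admission rates.
- Longitudinal 2-level models for immune competence, in which "the profile of within-person changes over time in antibody and cytokine levels will form the major response and explanatory variables".

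Salivary IgA is a named outcome of question 5 in section vi: "Effects of time of colonisation and PCV on mucosal immunity (salivary IgA responses to Pnc CPS and OMPs) will also be assessed". Table 2 schedules it against both capsular polysaccharides (CPS) and outer membrane proteins (OMPs), at several ages up to 18 months.

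**The concern.** A quantity recorded as a percentage cannot enter a logistic model until it has been cut in two. The natural reading is detected against not detected, and the protocol gives no detection limit or other cut-off for IgA. Two groups with the same share of detectable samples but different IgA levels would then look alike. Where most infants have detectable IgA, the model has little left to compare.

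The regression list matters for question 5. PCV is randomised, but age at colonisation is not. Comparing infants colonised early and late calls for adjustment for crowding, housing and town or country, and these regressions are where the protocol makes such adjustments. The cytokine entries show that the authors plan a level and a detection analysis side by side when they want both.

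**Working it through.** **1. The texts side by side.**

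| Response | Scale recorded | Level model in the covariate list | Detection model in the covariate list |
|---|---|---|---|
| Serum IgG | concentration | linear | none |
| Cytokines | level | linear | logistic |
| Salivary IgA | % of total salivary IgA | none | logistic |

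IgA is the only continuous assay result in the list without a level model.

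**2. The plan's own power figure.** There is none for IgA. The nearest is serum seroprotection in section vii: 70% against 50%, 80% power, at least 90 evaluable per group. The two-sided 5% pooled test of two proportions has

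power = Φ{ [ |p1 − p0|·√n − 1.96·√(2·p̄(1 − p̄)) ] / √(p0(1 − p0) + p1(1 − p1)) }.

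With n = 90, p0 = 0.50, p1 = 0.70 and p̄ = 0.60: (0.20 × 9.487 − 1.96 × 0.6928) / 0.6782 = 0.795, and Φ(0.795) = 78.7%. With n = 100 the result is 82.8%. The stated 80% is reproduced, so the same formula and n are used below.

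**3. Assumptions for the illustration.** 90 per group; log IgA normal with equal SD in both groups; samples below one detection limit unquantified; two-sided 5%. The share detectable in controls is not given and is varied from 10% to 80%.

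**4. Shift that gives the detection test 80% power.** For each control share p0, solve the formula for p1. The shift in SD units is z(p1) − z(p0), where z is the normal quantile. Example at p0 = 0.50: p1 = 0.703, p̄ = 0.6015, (0.203 × 9.487 − 1.96 × 0.6924) / 0.6773 = 0.84, power 80%. The shift is z(0.703) − 0 = 0.53 SD.

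**5. Power of level analyses on the same samples.** Normal data were simulated with that shift and cut at the implied limit (1,500 runs per row). Three tests were applied: the two-proportion test on detection, a Wilcoxon test with undetectable values tied, and a likelihood-ratio test from a left-censored normal (Tobit) model.

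| Detectable, controls | Detectable, other group | Shift (SD) | Detection test | Wilcoxon | Tobit | Gain (points) |
|---|---|---|---|---|---|---|
| 10% | 25.9% | 0.64 | 82% | 84% | 86% | 2–3 |
| 20% | 38.9% | 0.56 | 82% | 84% | 86% | 3–4 |
| 30% | 50.3% | 0.53 | 81% | 86% | 87% | 5–6 |
| 50% | 70.3% | 0.53 | 81% | 92% | 93% | 11 |
| 70% | 87.0% | 0.60 | 80% | 98% | 98% | 18 |
| 80% | 94.0% | 0.71 | 81% | 99% | >99% | 18 |

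Gains are computed before rounding. The Monte Carlo 95% margin on one power figure near 85% is 1.96 × √(0.85 × 0.15 / 1500) = 1.8 points. Separate runs of the same design gave 1–2 points at 10%, 3–4 at 20%, 10–13 at 50% and 17 at 70–80%. Together: about 1 to 4 points at 10–20% detectable, 10 to 13 at 50%, and 17 to 18 at 70–80%.

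**6. Sensitivity to the assumed effect.** Now fix the shift instead and compare the detection test with a t-test on values floored at half the limit. The SD of 1 log unit is borrowed from serum IgG. At a shift of 0.418, where a fully observed level would have 80% power, the losses are about 2, 4, 6, 14 and 25 points at 10%, 20%, 30%, 50% and 70% detectable. At a shift of 0.6 they are about 2, 4, 5, 8 and 18. The pattern is the same but the size moves with the assumptions.

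**The case against.** The strongest reply is about scope, and it stands. The logistic clause belongs to the sentence on further covariate analyses. The principal t-tests do not exclude IgA percentage. The 2-level models speak of antibody levels, not IgG levels. Question 6(a), on the ontogeny of natural immunity, counts salivary IgA as part of humoral immunity under a heading on maturation of immune competence, so on a natural reading it goes to those level-based models. A reader might infer that detection replaces level for IgA throughout the trial; the protocol does not support that.

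A detection response also has some rationale. Salivary CPS antibody is described as low, and the background calls salivary responses modest after the primary series, whereas the ELISA cytokines are said to be readily detectable in most infants. This stands in part. Where few samples are detectable, the table shows that little is lost. But the remark on low concentrations concerns CPS antibody only, while IgA to the OMPs goes into the same logistic entry. Low values are also a reason to treat the undetectable ones as censored, not to drop the measured ones.

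A reader might also want one figure, such as a loss of 5 to 18 points. That cannot be derived from the protocol, which gives no SD, effect size, detection limit or detection rate for IgA, and at 10–20% detectable the gain falls below 5. The simulation compares two unadjusted groups of equal size, whereas the clause concerns adjusted regression; and Tobit is tested on data from its own model, though Wilcoxon is close to it throughout.

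Finally, the choice of censoring method could be left to a statistical analysis plan. But the protocol has not left the model open: it names logistic for IgA and no other.

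**Conclusion.** The point holds within the covariate regressions. There the only model named for salivary IgA is a yes/no one, although the measurement is continuous and cytokines are given both models. The adjusted analyses for question 5 would lose the level in infants with measurable IgA. The principal tests and the 2-level models are not affected.

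The direction is consistent in every scenario examined: the loss is small if salivary IgA is seldom detectable and substantial if half or more of control samples are. The step 5 figures are illustrations resting on the step 3 assumptions, not properties of this trial. The outcome is secondary, since the primary outcome is serum IgG at 2 months. This is a cheap improvement, not a threat to the main conclusions.

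**What to change.** In Data analysis, add salivary IgA level to the covariate regressions alongside the logistic model. The response would be the log of specific IgA as a percentage of total salivary IgA, with values below the detection limit treated as left-censored. A rank test would serve for simple group contrasts. Define what counts as detected, and keep the logistic model as the supporting analysis, as is already done for cytokines.

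The cost is about one sentence, with no new samples or assays. The small downside is the distributional assumption in the censored model, which the rank test avoids for unadjusted comparisons.
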